### Randomization

All patients who consent to participate and who fulfill the inclusion criteria will be randomized. Eligible participants will be randomly assigned to the IG and the CG based on a table of random numbers (https://www.sealedenvelope.com/). Results of random allocation will be placed in an opaque envelope.

### Blinding

Allocation details will be placed in opaque and sealed envelopes by a study coordinator and concealed from recruiters, data collectors and the group allocator. After recruitment and baseline data collection, the other study coordinator will open the envelopes and allocated participants. Due to the nature of the intervention, intervention conductors and participants will not be blinded to group allocation. The data collector will be masked to group allocation during data collection and the statistician will also be masked during data analyses.

### Interventions

#### Control group

Participants in the CG will receive usual prenatal and postnatal care. At the same time, they will be contacted by the researchers upon initial enrollment in the study but receive no further guidance and interventions.

#### Intervention group

The intervention of this study was constructed based on a literature review, qualitative interviews and group discussion. And the feasibility and importance of the intervention program were verified through two rounds of expert consensus based on the Delphi method [25].

Participants in the IG will be offered the breastfeeding promotion intervention model based on the SET. According to the SET, the intervention is designed in three parts: macro system, mezzo system and micro system. (1) Macro system: It mainly refers to the policies, institutions and culture that affect breastfeeding. This study can create a favorable breastfeeding atmosphere through activities such as introducing breastfeeding and childbirth-related policies and actively publicizing and reporting beneficial experiences of breastfeeding promotion. (2) Mezzo system: It refers to a small group of people including pregnant women. Hospitals, communities and families are important places for women throughout pregnancy, delivery and the postpartum period. This study will optimize the breastfeeding promotion intervention of hospital-community-family to achieve information sharing and joint management. Relying on the online WeChat mini program, it will be extended to offline services. (3) Micro system: Maternal individuals, as subjects, are the core of the social ecosystem. This study will provide social support to maternal individuals to reduce the incidence of depression and anxiety, improve the rate of breastfeeding, and promote maternal and child health. Details of the intervention are shown in Tables 1 and 2.

**Table 1 Tab1:** Breastfeeding promotion intervention model based on the Society Ecosystems Theory

	Time	Content
Macro system	First week after recruitment	**Introduction to policies:** Collect breastfeeding policy documents in China and present them to pregnant women and co-parents via online images and text, such as the Global Strategy for Infant and Young Child Feeding, 10 Measures to Promote Successful Breastfeeding (2018), Action Plan for Breastfeeding Promotion (2021–2025), Breastfeeding Guidelines for Infants up to the Age of 6 Months, National Nutrition Program (2017–2030), International Code of Marketing of Breast-milk Substitutes, Chinese national and local maternity leave policies.
	First week after recruitment	** Breastfeeding support facilities:** Pregnant women and those responsible for infant care are introduced to local breastfeeding support facilities, such as mother and baby rooms, Baby Friendly Communities and Hospitals.
	Recruitment to one month postpartum	** To create a good breastfeeding atmosphere:** Actively publicize and report the beneficial experience of breastfeeding through an interactive forum in the Ai You Wei WeChat mini-program; encourage pregnant women and mothers with breastfeeding experience to join the forums and share their experiences and feelings.
Mezzo system (Family)	First week after recruitment	**Join WeChat mini-program:** Invitation to pregnant women and co-parents to join the online platform “Ai You Wei”.
	First and second week after recruitment	** Breastfeeding lecture combined with theories and skills:** Introduce the breastfeeding theory and skills course to pregnant women and co-parents through a combination of online and offline formats. Details of breastfeeding lecture are shown in Table 2.
	First and second week after recruitment	**Course evaluation:** A combination of theory and skills courses to improve breastfeeding knowledge and skills. An online questionnaire at the end of each course assesses the learning of pregnant women and co-parents and provides additional guidance.
Mezzo system (Hospital)	Recruitment to one month postpartum	** WeChat group peer support:** Establish a WeChat group jointly managed by obstetricians and gynecologists, obstetric nurses, midwives, breastfeeding counselors, and community breastfeeding professionals, and invite pregnant women and those responsible for infant care to join the group chat to obtain consultation after recruitment.
	Within 48 h after delivery	** Postnatal hands-on instruction:** Instruct mothers and infant caregivers in obstetrics wards to experience on-site breastfeeding together; insist on early contact, early suckling, and early initiation of breastfeeding; provide instruction on feeding-related skills during hospitalization, including correct feeding positions, milking techniques, and so on.
Mezzo system (Community)	Seven days, twoweeks and 1-month postpartum	** Home visits:** Researcher and community members conduct postpartum home visits to mothers to provide guidance and education to mothers and those responsible for the upbringing of infants on breastfeeding, diet, exercise, and rest for new mothers, and to improve mothers’ breastfeeding knowledge and skills.
	Delivery to one month postpartum	** Group counseling:** Provide online group counseling (four sessions) to encourage peer-to-peer communication. Mothers’ meetings are organized with the participation of obstetricians and gynecologists, obstetric nurses and researchers, and group discussions are held for mothers and co-parents, who are encouraged to speak out about their inner feelings during breastfeeding.
	Delivery to one month postpartum	**Breastfeeding experience sharing:** Mothers with breastfeeding experience are invited to share the beneficial experience of breastfeeding online every week (four sessions).
Micro system	Recruitment to one month postpartum	**Individual counseling:** One-on-one personalized education or guidance throughout the intervention through home visits, phone calls, and online communication for ongoing breastfeeding.

**Table 2 Tab2:** Schedule of prenatal breastfeeding lectures including theories and skills

	Content
Theory Session 1	1. How is breast milk produced? 2. What factors affect the secretion of breast milk? 3. What are the ingredients in breast milk? 4. What are the characteristics of human milk? 5. What are the benefits of breastfeeding? 6. What do I need to prepare for breastfeeding? 7. How do I breastfeed? 8. How to tell if your baby is full?
Theory Session 2	1. How to prevent and manage common lactation problems? 2. How do mothers with flat or inverted nipples breastfeed? 3. How do mothers with sore or cracked nipples breastfeed? 4. How can breast swelling be prevented and relieved? 5. How do mothers breastfeed when they suffer from infectious/contagious diseases? 6. How should infants and young children be fed under special circumstances? 7. What should mothers eat in lactation period?
Skill Session 1	1. What are the common breastfeeding positions? 2. What are the best positions for babies to latch on to the breast and suckle? 4. What are the ways to promote milk secretion? 5. What are the ways to promote milk reflex? 6. How do I perform breast massage? 7. How do I perform hand milking?
Skill Session 2	1. how do I use a breast pump? 2. How do I store and warm breastmilk? 3. How do I breastfeed after work? 4. How do I wean properly? 5. Additional feeding knowledge of interest to pregnant mothers.

1. Format: online Tencent meeting; duration: 1 h per theory session and 40 min per skill session

2. The four sessions will be completed before the delivery, and the specific time of each class will be adjusted according to the availability of the participants and their families

3. Participants can invite at least one family member to attend each lecture

4.Lectures will be offered in small groups of five to ten participants per session

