### Sample size

The current EBF rate for infants under 6 months of age in China is 34.1% [3]. After the intervention, the rate is expected to increase to 60%, which was required by the *National Nutrition Plan (2017–2030)* [5]. Sample size was calculated for EBR in 6 months for a two-sided hypothesis test with a power of 90% and a significance level of 0.05. Therefore, according to the following formula, the study requires a minimum sample size of 76 (each group). Considering a 20% lost follow-up rate and 20% withdrawal rate because of failure to participate in the full intervention due to prematurity, a total of 218 participants will be needed for the study.$${n}_{1}={n}_{2}=\frac{{{[u}_{\alpha }\sqrt{2P\left(1-P\right)}+{u}_{\beta }\sqrt{{P}_{1}\left({1-P}_{1}\right)+{P}_{2}\left({1-P}_{2}\right)} ]}^{2}}{{(P1-P2)}^{2}}$$

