### Statistical analysis

Statistical analysis will be completed using SPSS (version 24.0). In order to compare the difference at baseline between the two groups, the two-sample t-test will be used for continuous variables and the χ^2^ test for classified data. Analyses of differences between two groups regarding maternal and neonatal morbidity outcomes, IIFAS, BKQ, BSES-SF, PAQ, PSAS-CN, EPDS and SSRS are evaluated in the same manner. In addition, one-way ANOVA analysis and two-sample t-test will be used to explore the influencing factors of the EBF rate. The data from the IIFAS, BKQ, BSES-SF, PAQ, PSAS-CN, EPDS and SSRS of the two groups at different time points (T0, T1, T2 and T3) will be tested using repeated measurement Analysis of Variance (ANOVA). For variables that have an interaction effect in repeated measurement ANOVA, a simple effect analysis will be carried out to further explore the effects of each factor. Cohen’s d will be reported to check the effect size. Cohen’s d will be used to evaluate the magnitude of difference between the two groups. According to the standard established by Cohen, the large, medium and small of the effect of d was divided into 0.8, 0.5, and 0.2 [48]. The randomized trial will use the statistical analysis “per protocol”. The significance level is set to less than 0.05 (double-tailed). P-values will be reported to four decimal places p-values and those less than 0.001 will be reported as p < 0.001.

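### Only the intervention arm is taught and counselled in groups, yet the sample size and named tests assume independent women; how much this matters depends on an ICC the protocol does not give

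*Protocol article*

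**What the plan says.** Randomization is of individual women, 1:1. After allocation the arms are handled differently:

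- **Intervention arm.** Four prenatal lectures are given online. The Table 2 notes say: "Lectures will be offered in small groups of five to ten participants per session". After delivery, the community part of Table 1 adds: "Provide online group counseling (four sessions) to encourage peer-to-peer communication". The same table lists mothers' meetings with group discussion and weekly experience-sharing sessions.
- **Control arm.** Usual prenatal and postnatal care, with contact at enrolment and no group component (Interventions, Control group).

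The Sample size section describes its basis as follows: "Sample size was calculated for EBR in 6 months for a two-sided hypothesis test with a power of 90% and a significance level of 0.05". It prints the standard formula for two independent proportions and arrives at 76 per arm, with no design effect or ICC. Under Statistical analysis, "the two-sample t-test will be used for continuous variables and the χ^2^ test for classified data" at baseline, and the same methods are applied to the morbidity outcomes and the scales. The scales over time go to repeated-measures ANOVA. None of these methods carries a term for lecture or counselling group.

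**The concern.** This is a partially nested design: intervention women are grouped after randomisation and control women are not. Women in one group share an instructor, classmates and discussion, and the counselling is meant to make them talk to each other. If that influences what they know, feel or do, outcomes within a group are positively correlated. The variance of the intervention-arm rate or mean is then larger than a test on independent women assumes.

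Two things are at stake. First, confidence intervals that ignore the grouping are too narrow, and the true type I error exceeds the nominal 0.05 for the scales and morbidity outcomes. The same holds for a simple two-proportion test of the exclusive breastfeeding (EBF) rate. Second, a test that respects the grouping has less than 90% power at the 76 evaluable women per arm on which the plan is built.

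**Working it through.** **Inputs.** From Sample size: P1 = 0.341, P2 = 0.60, two-sided α = 0.05, power 90%, 76 per arm before losses and 218 in total (109 per arm). From the Table 2 notes: group size m = 5 to 10, midpoint 7.5. The ICC is not in the document, so 0.01 to 0.10 is an assumed range. Equal group sizes, and one group per intervention woman, are also assumed.

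**Step 1: reproduce the plan's figure.** P = (0.341 + 0.60)/2 = 0.4705.

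- 1.960 × √(2 × 0.4705 × 0.5295) = 1.3835
- 1.2816 × √(0.341 × 0.659 + 0.60 × 0.40) = 0.8736
- n = (1.3835 + 0.8736)² / 0.259² = 75.95, so 76 per arm.

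The stated figure is reproduced, and it contains no allowance for clustering.

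**Step 2: inflate the intervention arm only.** The design effect is DE = 1 + (m − 1) × ICC, and the control arm is left unchanged. At n per arm:

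- Power of a test that allows for group = Φ{[0.259 − 1.96 √(P(1−P)(1+DE)/n)] / √([P1(1−P1) + DE·P2(1−P2)]/n)}
- Type I error of the test that ignores group = 2[1 − Φ(1.96 / √((1+DE)/2))]

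Worked example with m = 7.5, ICC = 0.05, n = 76:

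- DE = 1 + 6.5 × 0.05 = 1.325.
- The standard errors are 0.0873 (null) and 0.0845 (alternative).
- (0.259 − 0.1711)/0.0845 = 1.04, so power is 85.1%.
- For type I error, 1.96/√1.1625 = 1.818, giving 6.9%.

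**Step 3: the range at 76 per arm (m = 5 / 7.5 / 10).**

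| ICC (assumed) | DE | Power allowing for group, % | Type I error ignoring group, % |
|---|---|---|---|
| 0 | 1 | 90.0 | 5.0 |
| 0.01 | 1.04 / 1.065 / 1.09 | 89.4 / 89.1 / 88.7 | 5.2 / 5.4 / 5.5 |
| 0.02 | 1.08 / 1.13 / 1.18 | 88.8 / 88.1 / 87.3 | 5.5 / 5.8 / 6.0 |
| 0.05 | 1.20 / 1.325 / 1.45 | 87.0 / 85.1 / 83.2 | 6.2 / 6.9 / 7.7 |
| 0.10 | 1.40 / 1.65 / 1.90 | 83.9 / 80.1 / 76.3 | 7.4 / 8.9 / 10.4 |

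These are normal approximations. With few groups (76/10 is about 8), a small-sample reference distribution would lower power somewhat further.

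**Step 4: allow for losses after the lectures.** Table 1 puts the lectures in the first two weeks after recruitment. If the planned losses come later, a group that started with 5 / 7.5 / 10 women has on average 76/109 of them left, about 3.5 / 5.2 / 7.0. At ICC 0.05 and 76 per arm, power is then 88.2 / 86.8 / 85.5% and type I error 5.7 / 6.2 / 6.8%. If some losses precede the lectures, the truth lies between these figures and the table.

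**The case against.** The strongest reply is that the protocol gives no ICC and offers several reasons to expect a small one:

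- Class times follow the availability of participants and families, so a woman may sit with different classmates each time. Fixed lecture groups are not stated, nor is the size of the counselling groups.
- The lectures total 2 × 1 h + 2 × 40 min = 3 h 20 min, are given before delivery, and precede a 6-month outcome.
- Bedside instruction, three home visits and one-on-one counselling come in between, and implementers are uniformly trained.

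All of this stands as a limit on size. It does not show that the correlation is zero. The counselling is meant to work through contact between mothers, and the lecture content is close to what the knowledge scale measures.

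A second reply is that Statistical analysis names no explicit between-arm test for the EBF rate, and that an analysis plan not shown here may add a group term. The first part is correct: the independent two-proportion test is implied by the sample-size formula, not named. The second part is possible, but the sample size is fixed in this document, and no later plan can use group membership that was never recorded.

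A third reply is that 109 per arm leaves slack. If nobody were lost, power would be 92% or more everywhere in the table's grid except m = 10 with ICC 0.10 (89.6%). However, the protocol assigns that margin to losses, and extra women do not repair type I error, which depends on the design effect and not on n.

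**Conclusion.** The structural point holds. Only one arm is group-delivered, while the sample size and the named tests assume independent women. The direction is certain for any positive ICC: type I error above 0.05 for tests that ignore group, and power below 90% at 76 evaluable per arm.

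The size is not established. It is minor at ICC 0.01–0.02 and becomes material from about 0.05, less so if groups shrink after the lectures. All figures assume one stable group per woman, which the document does not state, and changing membership may weaken the clustering.

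A reader might infer that the trial's p-values are definitely too small and that 90% power is definitely not delivered, or that 83–87% is the true power. The documents support neither reading, because each needs a particular ICC and none is given. Nor can the document be said to specify a faulty EBF test, since it names no between-arm test for that outcome.

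The point still merits a change, because the error would favour the intervention and the remedy is cheap.

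**What to change.** 1. Record, for each intervention woman, the lecture group first assigned and the counselling group. Fixed groups need not be imposed where scheduling prevents them. The recording has to be done as the sessions are delivered.
2. Analyse the EBF rate and the scales with a method that allows for group in the intervention arm only, each control woman being her own cluster. Suitable choices are a GEE with cluster-robust standard errors and a small-sample correction, or a partially nested mixed model. Report the estimated ICC.
3. In Sample size, state that 90% power assumes no clustering, and give power at 76 per arm over a declared ICC range, for example 0.01 to 0.10. Do not put a single replacement figure in its place.

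The cost is a small addition to data collection for group membership, a change of analysis wording, slightly wider confidence intervals and a less favourable stated power. No extra enrolment is asked for. If the ICC proves close to zero, little is lost.

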#### Intervention personnel training

Prior to the start of the study, the intervention implementers will undergo uniform training and assessment. Criteria for inclusion of intervention implementers include healthcare personnel with (1) intermediate or higher job title, (2) working in obstetrics and gynecology for ≥ 5 years, and (3) basic knowledge of breastfeeding nursing guidance. Training content and methods: (1) lectures on breastfeeding-related theories and skills; (2) self-study and online learning: theoretical knowledge and related materials, such as the *Global strategy for infant and young child feeding* [1], *Guide to infant feeding and nutrition* [26], and *Breastfeeding guidelines for infants within 6* *months of age* [27]. (3) simulation scenario: hands-on breastfeeding instruction. Assessment methods: (1) self-assessment: evaluation using the breastfeeding knowledge questionnaire (BKQ); (2) peer assessment: test questions on knowledge of breastfeeding theories and skills; (3) simulation method: simulated lectures and hands-on instruction on breastfeeding.

### Data collection

#### Basic information questionnaire

A researcher-designed questionnaire of socio-demographic information will be used to collect basic information about participants, including gestational age, number of pregnancies, parity, education level, family monthly income, employment status, length of maternity leave, co-parenting members, conception mode at baseline; and delivery mode, weeks of delivery, time of breastfeeding initiation, separation of mother and infant, and presence of comorbidities at 1 month postpartum.

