**Methods/design:**

The study is a single-blind, parallel design, randomized controlled trial with an intervention group (n = 109) and a control group (n = 109) that compares the effect of a breastfeeding promotion intervention model based on the society ecosystems theory with usual prenatal and postnatal care. The intervention covers macro- (policy, culture), mezzo- (family-hospital-community) and micro- (biological, psychological and social) systems of the maternal breastfeeding process. Infant feeding patterns, neonatal morbidity and physical and mental health of antenatal and postpartum women will be collected at baseline (28 to 35 weeks of gestation), 1-, 4-, and 6-month postpartum.

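### The search for factors influencing exclusive breastfeeding uses single-factor tests that cannot account for arm, so a variable that the intervention shifts may show an association that only reflects allocation

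*Protocol article*

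**What the plan says.** The Statistical analysis section states that "one-way ANOVA analysis and two-sample t-test will be used to explore the influencing factors of the EBF rate". It does not list the candidate factors, does not mention arm in this sentence, and does not say whether the arms are pooled or analysed separately.

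The Basic information questionnaire section names items collected at baseline (parity, education, income and others) and then a second group: "delivery mode, weeks of delivery, time of breastfeeding initiation, separation of mother and infant, and presence of comorbidities at 1 month postpartum". Under Blinding, envelopes are opened after baseline data collection, and the Abstract places baseline at 28 to 35 weeks of gestation. The second group is therefore measured after randomisation.

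Table 1, in the hospital part of the mezzo system, tells staff within 48 hours of delivery to "insist on early contact, early suckling, and early initiation of breastfeeding". The Aim section adds that the trial seeks to improve breastfeeding attitudes, knowledge and self-efficacy.

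The Sample size section sets EBF at 34.1% under usual care and 60% under the intervention, for a "two-sided hypothesis test with a power of 90% and a significance level of 0.05".

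**The concern.** A one-way ANOVA or a two-sample t-test has one grouping factor. If that factor is EBF status, or the candidate variable, there is no room for arm.

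The trial is designed so that EBF differs by arm. It also intends to move several measured quantities: time of initiation, and follow-up knowledge, attitude and self-efficacy scores. Any quantity that differs by arm will be correlated with any outcome that differs by arm once the arms are put together, even if the two are unrelated within each arm. If such quantities are among the candidates, some of the reported influencing factors could be by-products of allocation. Readers would take them as targets for future programmes.

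This is separate from the poor fit of these tests to a yes/no outcome. A logistic model without arm would have the same fault.

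**Working it through.** **Inputs from the article.** EBF 34.1% (control) and 60% (intervention); 76 per arm required, 109 per arm randomised; two-sided 0.05.

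**Input assumed.** The size of the shift that the intervention causes in a candidate variable. The article gives none, so a range is shown. The candidate has no association with EBF inside either arm.

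**1. The plan's own figure.** With P = (0.341 + 0.60)/2 = 0.4705, the printed formula gives [1.96 × √(2 × 0.4705 × 0.5295) + 1.2816 × √(0.341 × 0.659 + 0.60 × 0.40)]² / 0.259² = (1.3835 + 0.8737)² / 0.0671 = 75.9, so 76 per group. This reproduces.

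**2. How allocation leaks into a pooled test (continuous candidate).**
- Share of intervention women among those with EBF: 0.60/(0.341 + 0.60) = 0.638.
- Share among those without: 0.40/(0.659 + 0.40) = 0.378.
- A candidate shifted by d SD therefore differs by d × (0.638 − 0.378) = 0.26d between EBF and non-EBF women, with no effect of its own.
- At 109 per arm, expected numbers are 109 × 0.941 = 102.6 with EBF and 109 × 1.059 = 115.4 without.
- SE = √[(1 + 0.231d²)/102.6 + (1 + 0.235d²)/115.4], where 0.231 = 0.638 × 0.362 and 0.235 = 0.378 × 0.622.
- For d = 0.5: difference 0.130, SE 0.140, ratio 0.93. The chance of |Z| > 1.96 is P(Z > 1.03) + P(Z < −2.89) = 0.152 + 0.002 = 15.4%.

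**3. False-positive rate of the pooled t-test, by simulation (6,000 trials per setting), with the formula alongside.**

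| Assumed shift | 76 per arm, simulated | 109 per arm, simulated | 109 per arm, formula |
|---|---|---|---|
| 0 SD | 5.1% | 4.9% | 5.0% |
| 0.2 SD | 6.0% | 6.5% | 6.7% |
| 0.5 SD | 11.9% | 15.8% | 15.4% |
| 0.8 SD | 22.2% | 30.1% | 29.8% |

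**4. Binary candidate, such as early initiation yes/no.** Take 40% versus 70% by arm.
- Intervention share among yes: 0.7/1.1 = 0.636, so pooled EBF is 0.341 + 0.259 × 0.636 = 50.6%.
- Intervention share among no: 0.3/0.9 = 0.333, so pooled EBF is 0.341 + 0.259 × 0.333 = 42.7%.
- The spurious difference is about 8 percentage points.

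| Assumed prevalence, control vs intervention | 76 per arm | 109 per arm |
|---|---|---|
| 50% vs 50% | 4.7% | 5.3% |
| 40% vs 50% | 6.1% | 6.8% |
| 40% vs 60% | 9.3% | 12.0% |
| 40% vs 70% | 16.5% | 21.2% |
| 40% vs 80% | 25.9% | 34.1% |

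**5. Two controls.**
- With a Mantel-Haenszel test stratified by arm, the rate was 4.5% to 5.3% in every binary setting, so accounting for arm removes the problem.
- If the intervention does not change EBF (47% in both arms, candidate 40% versus 70%), the pooled test stays at 4.8% and 4.9%. Both conditions are needed: the candidate must shift, and EBF must differ by arm.

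**The case against.** The strongest reply is that much of this is inferred. The article does not list the candidates, does not say that the arms are pooled, and calls the analysis an exploration. A full protocol or analysis plan may settle all three. That stands, and it is why the point is conditional. It does not answer everything, because the article does name the tests, and neither has a term for arm. Running them within each arm would avoid the problem, but the article does not say so.

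A reader might go further in three ways that the documents do not support.

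- *That the 1-month items are treated as baseline data.* They share a questionnaire heading, but the text states the two collection times separately, and the balance tests are limited to differences at baseline.
- *That the treatment effect will be over-adjusted.* No covariate-adjusted comparison of the arms is planned.
- *That variables with no effect will generally look like determinants.* Even at the largest shifts tabulated, about two thirds of trials would not flag such a variable, and at 0.2 SD the rate is close to nominal. Parity, education, income and the other baseline items are independent of arm by randomisation and keep 5%. Delivery mode, weeks of delivery and comorbidities are not stated intervention targets.

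**Conclusion.** The point holds in a limited form. As written, the influencing-factor analysis cannot take account of arm. For a candidate that the intervention shifts, a pooled test has an inflated false-positive rate: at 109 per arm about 7% at 0.2 SD, 15% to 16% at 0.5 SD and 30% at 0.8 SD, against a nominal 5%.

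This rests on four conditions: the planned EBF difference is realised; the arms are pooled; post-randomisation variables such as initiation time or follow-up scale scores are among the candidates; and the shift is of the assumed size. Only the planned EBF difference is given in the article. That the intervention aims to shift some of these variables is also the trial's own premise.

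The consequence is confined to a secondary, exploratory analysis. The randomised comparison of EBF and the sample size are untouched.

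**What to change.** In the Statistical analysis section, replace the ANOVA and t-test sentence on influencing factors with an exploratory model for the binary EBF outcome, such as logistic regression, that includes arm or is stratified by arm. Name the baseline items as the candidate determinants. If any post-randomisation variable is examined, including time of initiation and the follow-up knowledge, attitude and self-efficacy scores, report it only as an association given arm.

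Comparing time of initiation between arms as a process measure would be a useful but optional addition.

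The cost is a change of wording and slightly more analysis work, with no new data. The downside is fewer candidate determinants.
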